**Table Taba:** 

Agitation, including aggressive behavior or hostility	Obsessive-compulsive symptoms
Attention problems	Restlessness
Bad or vivid dreams	Sleepwalking
Depression	Stuttering
Disorientation or confusion	Suicidal thoughts and actions
Feeling anxious	Tremor or shakiness
Hallucinations	Trouble sleeping
Irritability	Uncontrolled muscle movements
Memory problems	

In addition, while to our knowledge there have been no human reports of impaired wound healing associated with montelukast use, there have been studies utilizing different animal models that have reported the potential for delayed healing. The animal studies that reported impaired healing or decreased angiogenesis used doses of 10 mg/kg/day [48–50] whereas other studies reported improved healing characteristics at either the same dose (10 mg/kg/day, [51, 52]) or lower dose (3 mg/kg, [53]). In the one study that assessed the effects on human tendon fibroblasts, the effect did appear to be dose dependent with an increased effect on fibroblasts with increasing doses [54]. We do not expect wound complications since our study will be using a dosage of approximately 0.14 mg/kg/day (10 mg/day assuming an estimated body mass of 70 kg), and there have been no clinical cases reported to date; however, we will closely monitor the surgical incisions for signs of delayed healing at all routine standard of care visits in addition to the 1-month study visit. Furthermore, postoperative montelukast will not be initiated until 10 days following surgery once there is evidence of sufficient wound healing. This is the time frame during which patients undergoing ACL reconstruction routinely have their sutures removed and begin to shower without having the wound covered. Should a patient not have adequate wound healing at the 10-day time point, they will not be randomized and will be withdrawn from the study.

Breaking the randomization code will be performed by the study’s medical officer and will occur if it is necessary for the care of the subjects. For example, if an adverse event or serious adverse event occurs with a subject and knowledge of the drug randomization would be important for clinical care or to determine appropriate treatment, then the principal investigator will break the code and the subject will be withdrawn from the study. If a subject discontinues the study for any reason prior to the 6-month follow-up visit, then the collected data will be evaluated but not included in the analysis and a replacement subject will be enrolled in the study. There are no provisions for ancillary or post-trial care.

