#### Safety monitoring

A safety review of treatment group will be performed with safety endpoints being monitored at each study visit. Due to an FDA black box warning related to montelukast, we will utilize the Patient Health Questionnaire-9 (PHQ-9) to quantify depressive symptoms and suicidality at all clinic-based study visits. The PHQ-9 is a validated, self-administered screening instrument that asks patients to select how often they have been bothered by specific symptoms in the last 2 weeks [46, 47]. The PHQ-9 consists of 9 questions that parallel the diagnostic criteria for Major Depression Disorder from the Diagnostic and Statistical Manual of Mental Disorders. Each item is scored from 0 to 3 with 3 representing more severe symptoms. PHQ-9 scores range from 0 to 27, and scores of 15 or greater are indicative of severe depression [46]. After providing informed consent, patients will complete a baseline PHQ-9 questionnaire. Should the subject have a PHQ-9 ≥ 15 at baseline, they will be withdrawn from the study. If the patient is not currently being observed and/or treated for depression, they will be then referred to their primary care physician or mental health professional for evaluation. The PHQ-9 also has a question that is specific to suicidal thoughts. Should the subject endorse suicidal ideation at baseline, the subject will be withdrawn from the study prior to initiating treatment and a “warm hand-off” will be performed and a risk assessment will be performed by the local psychologist that is a part of the study team.

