##### Study stopping rules

Neuropsychiatric symptom severity and suicidality will be monitored closely within study procedures and reviewed weekly by the study’s medical officer and the principle investigator, and referrals for appropriate levels of care will be done as needed. At all study postoperative follow-up visits, subjects will complete the PHQ-9. Similar to the enrollment screening procedures, treatment will be immediately stopped for subjects with scores ≥ 15 or if they endorse suicidal ideation. The subject will then be referred to their primary care physician, mental health professional, or the study’s local psychologist that is a part of the study team as described above. In addition, consistent with the FDA’s guidance [30], treatment will also be immediately stopped if patients experience a change or increase in any of the following behavior or mood-related changes:

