##### Blinding

The team member that prepared the randomization schedule will meet with the pre-specified unblinded study personnel prior to the site initiation visit. The unblinded personnel will then prepare sealed envelopes that contain each subject’s group assignment.

We will designate, a priori, study personnel that will be unblinded. These unblinded personnel will be directly involved with preparing the blinded medications and maintaining the drug log. The unblinded pharmacist/coordinator will access the actual treatment assignment but both blinded study personnel and the patient will not know the patient’s treatment assignment. Treatments will be prepared by designated unblinded personnel who will have no other patient contact.

Should an investigator become inadvertently unblinded, the principal investigator and medical officer will determine the extent of the unblinding and potential ramifications. If necessary, the investigator’s role may need to be altered to only include tasks affiliated with unblinded personnel. Should a patient become inadvertently unblinded, that patient’s data will continue to be collected for safety purposes; however, the data will not be used for the final analyses and a replacement subject will be enrolled. Unblinding of a subject(s) group assignment will be documented and will include an explanation of why the study medication was unblinded. Following data lock, group assignment can be unblinded and the unblinded information can be sent to the study participants at the discretion of the principal investigator.

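### Breaking the code for an adverse event removes the participant from the study, which on the most natural reading ends the remaining scheduled safety assessments (minor; few participants likely)

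*Protocol article*

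**What the plan says.** The protocol article has three kinds of rule that bear on this point.

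- **Code break for an event.** Study stopping rules, after the symptom table, allows the code to be broken when a participant's care requires it. The example given is an adverse or serious adverse event for which the allocation matters clinically: "then the principal investigator will break the code and the subject will be withdrawn from the study". The next sentence says that anyone leaving the study before the 6-month visit has the data already gathered evaluated, is left out of the analysis and is replaced.
- **Accidental unblinding of a patient.** The Blinding section says that such a patient's "data will continue to be collected for safety purposes". Those data are kept out of the final analyses, and a replacement is enrolled.
- **Stopping the drug only.** For a PHQ-9 score of 15 or more, or suicidal ideation, at a postoperative visit, Study stopping rules says "treatment will be immediately stopped for subjects with scores" at that level. It says nothing there about leaving the study.

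Safety capture is tied to visits. Safety monitoring describes "safety endpoints being monitored at each study visit", and Study stopping rules adds: "At all study postoperative follow-up visits, subjects will complete the PHQ-9".

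**The concern.** Unblinding for clinical care is a good reason to stop study drug and to treat later assessments as unblinded. It is not a reason to stop recording what happens to the participant. Whether an event resolves or recurs once the drug is off is useful safety information, and it matters most in someone whose event was serious enough to need the code.

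As written, that participant has less stated safety capture than one who learns the allocation by accident. The drug carries a boxed warning, and the trial plans 15 participants per group, so even one incomplete event history is a visible part of the safety record. What is at stake is the scheduled trial record of the event's course, not the participant's treatment.

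**Working it through.** The article gives no figure for the number of code breaks or the follow-up lost through them. The check is a comparison of wording followed by a count of visits.

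**Step 1: what does withdrawal mean in this article?**

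| Situation | Wording | Consequence |
|---|---|---|
| Suicidal ideation at baseline (Safety monitoring) | "the subject will be withdrawn from the study prior to initiating treatment" | Participation ends, before any drug |
| Wound not healed at day 10 (Study stopping rules) | "they will not be randomized and will be withdrawn from the study" | Participation ends, before randomization |
| High PHQ-9 or suicidal ideation after surgery (Study stopping rules) | "treatment will be immediately stopped for subjects with scores" | Drug stops |
| Patient unblinded by accident (Blinding) | "data will continue to be collected for safety purposes" | Safety follow-up kept |
| Code broken for an event (Study stopping rules) | "then the principal investigator will break the code and the subject will be withdrawn from the study" | Same verb as the first two rows, with no clause keeping follow-up |

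The article has one form of words for stopping the drug and another for keeping safety collection. The code-break rule uses neither. The first two rows concern people who never took study drug, so they are weaker evidence than the contrast with the third and fourth.

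**Step 2: which visits come after treatment starts?**

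- Start of treatment: "postoperative montelukast will not be initiated until 10 days following surgery", that is 10/30.44 = 0.33 month.
- Visits: months 1, 6 and 12 (abstract, Methods). MRI analyses numbers month 1 as visit 4 and month 12 as visit 6, so month 6 is visit 5.
- Cross-check: biomarkers are sampled on the day of surgery and at every postoperative study visit, and are analysed with four time points. 4 − 1 = 3 postoperative visits, which agrees.

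**Step 3: visits lost if withdrawal ends participation.**

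| Time of code break | Visits lost | Scheduled follow-up lost |
|---|---|---|
| Day 10 to month 1 | 3 (months 1, 6, 12) | 12 − 0.33 = 11.7 months, down to 12 − 1 = 11 |
| Months 1 to 6 | 2 (months 6, 12) | 12 − 1 = 11 months, down to 12 − 6 = 6 |
| After month 6 | 1 (month 12) | less than 6 months |

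If the safety follow-up kept after accidental unblinding applied here too, the number lost would be 0 in every row.

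Dosing ends at month 6 if counted from surgery, or at month 6.33 (6 + 0.33) if six months are counted from day 10. The last row therefore falls almost wholly after the drug has ended and matters least. I give no average across rows, because the article does not say how often or when codes would be broken.

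**The case against.** The strongest reply has four parts.

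1. **No sentence says that safety collection stops.** This is true. It is an inference from wording, the clause sits inside an example, and the other uses of the withdrawal phrase come before randomization. The inference is still the natural one, because the article uses different words when it means drug only and says so when it wants safety data to continue.
2. **A condensed article may leave event follow-up to the full protocol.** It may, and the full protocol could follow events to resolution. But the article is not silent here: it gives a positive instruction to withdraw the participant. If the full protocol says otherwise, the article's sentence misstates it and needs the same edit.
3. **Little information may be lost.** Much of this stands. Code breaks should be rare. Incisions are also checked at routine care visits, and neuropsychiatric symptoms are reviewed weekly. After a break just past month 1 the next study visit is about five months away, so the schedule tracks resolution only coarsely. That is why the fix asks for the outcome of the event as well as attendance.
4. **Deleting the withdrawal clause opens another gap.** This stands in full. Replacement is triggered by leaving the study before month 6, and the exclusion in the Blinding section covers accidental unblinding only. A participant kept on after a code break would have no stated analysis or replacement status unless the fix supplies one.

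A reader might also infer that the two unblinding rules contradict each other. They do not: their triggers differ, and both can be followed. Nor do the documents support the inference that everyone who stops drug for a neuropsychiatric reason is lost to follow-up. Stops without a code break are worded as drug-only and are outside this point.

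**Conclusion.** The point holds as a minor, cheaply corrected weakness. On the most natural reading, an event-driven code break ends scheduled trial safety assessment and costs one to three of the visits at months 1, 6 and 12, depending on timing. Three is the maximum and needs a break before month 1.

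This rests on one assumption, that withdrawal ends participation for a treated participant as it does for those removed before treatment. The number affected is not given and is probably very small. No power or sample-size figure changes.

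It would go too far to say that the participant loses medical care. The article disclaims ancillary and post-trial care, but routine postoperative care does not depend on being in the study. What may be lost is the planned trial record of how the event evolved.

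**What to change.** In Study stopping rules, replace the withdrawal half of "then the principal investigator will break the code and the subject will be withdrawn from the study" with wording such as: *study drug will be permanently stopped and, unless consent is withdrawn, the subject will continue the remaining scheduled visits for safety purposes (including the PHQ-9 and the outcome of the event)*.

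In the same place, state two things:

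- whether this participant's later data, including the 12-month MRI that supplies the outcome named in Power analysis, enter the intention-to-treat analysis;
- whether a replacement is enrolled, so that the rule repeated under Randomization stays clear.

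The drug-only stopping rule for PHQ-9 scores and suicidal ideation needs no change.

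The cost is a short amendment at the two institutional review boards named in Design and setting. Each affected participant attends the one to three visits already planned for them, and the visits and the PHQ-9 are already in the schedule.

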#### Blinding procedures

The principal investigator, patients, and assessors will be blinded to group assignment. Using broad and previously established enrollment criteria, we hope to reduce selection bias to a minimum while protecting potentially vulnerable individuals through the exclusion criteria. Procedural bias and measurement bias will be reduced by the blinded data analysis.

##### Randomization

Following informed consent and after successfully being screened into the study based on intraoperative findings and adequate wound healing 10 days following surgery, subjects will be randomized to one of two groups. The randomization schedule will be made by a predesignated unblinded study team member that will not be involved in data collection or analysis. Using a random number generator, allocation of drug or placebo will be by permutated random block size, ensuring that approximately equal numbers of subjects will be treated with drug or placebo in the unlikely event that the study will need to be terminated prematurely. Should a subject discontinue the study for any reason prior to 6-month follow-up visit, then the collected data will be evaluated but not included in the analysis and a replacement subject will be enrolled in the study. As such, the randomization schedule will be prepared for 40 potential participants despite having a target enrollment of 30 participants to ensure adequate power.

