### Design and setting

This is a multicenter, superiority RCT with parallel group assignment and 1:1 allocation ratio to assess the use of montelukast after ACL reconstruction. The study has been approved by both the University of Kentucky and University of California San Francisco institutional review boards. Details of the study design are set out in Fig. 1 according to the Standard Protocol Items: Recommendations for Interventional Trials (SPIRIT) Statement [41]. The SPIRIT Checklist can be found in Additional file 1. Participants will be enrolled at two academic medical centers (University of Kentucky and University of California San Francisco) with study-related analyses being performed at the Cleveland Clinic and Duke University. Important protocol modifications will be communicated to the investigative team through regular weekly meetings. It will be the PI’s responsibility to update participants or trial registries on any protocol modifications.

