#### Data monitoring

Clinical site monitoring will be conducted by a member of the research team, [name], to ensure that the rights and well-being of trial participants are protected, that the reported trial data are accurate, complete, and verifiable, and that the conduct of the trial follows the currently approved protocol/amendment(s), with International Conference on Harmonisation Good Clinical Practice (ICH GCP), and with applicable regulatory requirement(s).

Remote clinical monitoring will be performed within 2 weeks following enrollment of the first subject, and repeated bi-annually (6 months) thereafter. Remote monitoring will include comprehensive, 100% data verification. Independent audits will not be conducted by the study sponsor to ensure monitoring practices are performed consistently across all participating sites as this is a single-site study.

[name] will conduct monitoring to verify that (a) the rights and well-being of human subjects are protected; (b) the reported trial data are accurate, complete, and verifiable from source documents; (c) the conduct of the trial is in compliance with the currently approved protocol/amendment(s), Food and Drug Administration (FDA) regulations and ICH guidelines; (d) ensure the quality and integrity of clinical study data; and (g) evaluate the progress of the study and ensure completion of the clinical study in a timely manner.

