#### Rigor and reproducibility

Biomarker data collected will be analyzed with respect to variability, linear range of standard, and need for repeat analyses. Controls provided with commercially available ELISA kits will be used with every run. For assays for which no control is available or provided, aliquots of serum from normal human subjects have been aliquoted and frozen at – 80 °C for this purpose. Each assay day, a fresh aliquot of this control serum is thawed and used on every plate to calculate intra- and inter-assay variance of the assay. In addition to the standard curve run in duplicate for each assay, this control will be run with each assay and the results used to determine the precision of the assay and to establish an acceptable control range for the assay. The mean of the control sample for all assays plus or minus two standard deviations is defined as the acceptable control range. Any samples on a plate in which the control falls outside of this range will be excluded and repeated. Samples will be run in duplicate and reanalyzed if the coefficient of variation is greater than 15%. For values that are below the level of detection as defined by the lowest standard, a value equivalent to 0.5 lowest limit of detection will be recorded and used for statistical analyses. To ensure data quality and fidelity, all data collection and analysis procedures will be detailed in a structured manual. The full research team will attend half-day training sessions both prior to study initiation and following enrollment of the first three patients have been enrolled to identify unforeseen issues that may arise and will also convene quarterly throughout the study period.

For cartilage T_1ρ_ and T_2_ quantification, we have published excellent scan/re-scan reproducibility in human subjects with coefficients of variation (CV) < 4% for single vendor settings [74] and CV < 10% for multi-vendor settings [75] using the MAPSS sequences [76]. Longitudinal CVs of monthly collected phantom T_1ρ_ and T_2_ have been reported < 3% [74]. In this study, a T_1ρ_ and T_2_ phantom will be scanned monthly at each site for the duration of the proposed study. SNR, intra-day reproducibility, and inter-day reproducibility will be quantified. Longitudinal data will be examined for any potential shift of quantified parameters. If more than 3% of relaxation time shift is observed, acquisition of subjects will be put on hold until discrepancies can be resolved.

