#### Relevant covariates

Covariates known to influence the selected biomarkers will be collected and included as covariates in the statistical analyses which include patient age, biological sex, and race [77]. The location of significant differences will be determined using post hoc tests with a Bonferroni correction.

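### Two enrolling and scanning centres, but site is not named as a stratification factor and appears in no stated model or covariate list

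*Protocol article*

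**What the plan says.** - **Sites.** Design and setting: "Participants will be enrolled at two academic medical centers", in a "superiority RCT with parallel group assignment and 1:1 allocation ratio". MRI analyses has patients scanned at both enrolment sites. The Data monitoring section nevertheless justifies the absence of independent audits "as this is a single-site study".
- **Allocation.** Randomization: "allocation of drug or placebo will be by permutated random block size", and "the randomization schedule will be prepared for 40 potential participants despite having a target enrollment of 30 participants". No stratification factor is named, and the text does not say that there is none.
- **Models.** Primary aim analysis gives a 2 × 4 repeated-measures ANOVA (group × time) for PGE2 and MCP-1. Secondary aim analysis gives a 2 × 2 version for T1ρ, T2 and bone shape, a 2 × 4 version for CTXII and CTXIα, and chi-square or Fisher tests for MOAKS. Site is in none of these.
- **Covariates.** Relevant covariates lists those that "include patient age, biological sex, and race".
- **Scanner control.** Rigor and reproducibility provides for monthly phantom scans at each site and the rule "If more than 3% of relaxation time shift is observed, acquisition of subjects will be put on hold". It also cites published reproducibility of "CV < 10% for multi-vendor settings".

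**The concern.** Site is part of the design, and with 30 patients chance can leave the arms with clearly different site mixes. Any site-related difference in the 1-to-12-month T1ρ change would then enter the treatment estimate, and under the stated models it could not be adjusted for. Even with a balanced site mix, site variation that no model term absorbs stays in the error term.

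The outcome used for power is a within-patient change, so a fixed offset between scanners drops out if each patient is scanned at the same site both times. Two things do not drop out: a shift at one site between a patient's two scans, and a real difference between sites in how much T1ρ changes. The plan treats scanner shift as a risk worth monthly checks, but a shift below 3% triggers no hold. The covariate list is written into the article, so the omission of site is visible there and is more than an unreported detail.

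**Working it through.** **1. The plan's own power.** Inputs from Power analysis: 15 per group, difference 3.09 ms, SD 2.86 ms. Alpha and sidedness are not stated; two-sided 0.05 is assumed. Effect size = 3.09/2.86 = 1.08. Noncentrality = 1.08 × √(15/2) = 2.96. The noncentral t with 28 df gives 81.5%, as stated.

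**2. Chance of site imbalance.** Assume 15 patients per site, 15 per arm and no stratification. If the two sites' patients arrive in mixed order, the number of one site's patients in the drug arm is approximately hypergeometric.

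- P(10/5 or worse, either direction) = 2 × Σ(k = 10 to 15) C(15,k)² / C(30,15) = 2 × 11,099,510 / 155,117,520 = 14.3%.
- Simulating permuted blocks of 2, 4 or 6 (sizes assumed) gives about 13%.
- If the sites enrol 20 and 10, the hypergeometric chance of a site-share difference of a third or more is 5%.

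**3. Shift in the estimate.** The documents give no mean T1ρ, so 35–50 ms is assumed. Let s be the difference between sites in mean change. For an upper-limit illustration, suppose every patient at one site carries the full 3% and nobody at the other carries any:

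- s = 0.03 × 35 = 1.05 ms to 0.03 × 50 = 1.5 ms.
- Shift in the treatment estimate at a 10/5 split = s × (10/15 − 5/15) = s/3 = 0.35 to 0.5 ms.
- Relative to the target: 0.35/3.09 = 11% to 0.5/3.09 = 16%.
- Relative to one standard error of the difference, 2.86 × √(2/15) = 1.04 ms: 0.34 to 0.48.

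**4. Power without a site term.** If 2.86 ms is the within-site SD and the sites are equal in size, the SD that the analysis sees is √(2.86² + s²/4).

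| s (ms) | SD (ms) | Power, 28 df |
|---|---|---|
| 0 | 2.86 | 81.5% |
| 1.05 | 2.91 | 80.2% |
| 1.5 | 2.96 | 78.9% |

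**5. Type I error.** In 10,000 simulated trials per setting, with unstratified allocation and no site term, the rejection rate under the null was 4.9%, 5.3% and 4.7% for s = 0, 1.2 and 2.4 ms. It is not inflated.

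**6. Cost of a site term when site explains nothing.** With site exactly balanced over arms, 27 df gives 81.4%. With 15 per site, the best possible split is 8/7, which gives 81.2%. If the site term is added but allocation is not stratified, chance imbalance brings average power to about 80%. Stratification therefore keeps the adjustment nearly free.

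**The case against.** The strongest reply is that the article condenses a fuller protocol and is silent on stratification. Sealed envelopes and a drug service at each institution fit per-site lists as well as a single list. That stands: a reader might infer that allocation is not stratified by site, but the text supports only that no such stratification is described.

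The size also rests on an extreme case. The 3% is a phantom hold limit and not an expected drift; the article cites longitudinal phantom variation below 3%. Recruitment is spread over a year, so a step shift would affect only patients whose two scans straddle it. The documents give no mean T1ρ. This stands too, and it is why the figures in step 3 are an upper-limit illustration for drift at one site.

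Other stronger readings also lack support:

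- The multi-vendor figure might suggest different scanners at the two sites. No vendor is named for either site, and one set of acquisition parameters is given for both.
- Separate drug services might look like a source of bias. Each prepares both drug and placebo, so they do not bias the comparison by themselves.
- Site might be said to explain 10–20% of the variance of change, with large power gains from adjustment. No figure in the article supports such a share.
- Drifts of 3% in opposite directions would double the shift in step 3, but they need both scanners at the limit at once.

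It can also be said that the covariate list concerns factors known to influence the biomarkers and need not be the whole T1ρ model. That is fair, but no other passage brings site into any model.

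**Conclusion.** The point holds in a limited form. Enrolment and scanning take place at two centres, while site is not named in the randomisation text and is missing from the stated models and covariates. The consequence is lost precision and possible chance confounding in the single trial run; it is not an inflated error rate or a systematic bias.

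A 10/5 or worse site split has about a 13–14% chance, given 15 patients per site and no stratification. The shift of 0.35–0.5 ms further assumes a mean T1ρ of 35–50 ms and a full 3% shift in every patient at one site. The power of 79–80% assumes that same shift and that 2.86 ms is the within-site SD. A true site difference in change would act in the same way, but its size cannot be taken from the documents.

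The effect is modest, but the remedy costs almost nothing. The single-site wording in Data monitoring contradicts Design and setting.

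**What to change.** - **Allocation.** Prepare a separate permuted-block list for each site, long enough for unequal recruitment, or state that this is already done.
- **Models.** Add site and site-by-time to the repeated-measures models (for T1ρ, equivalently, site in the change-score model). If allocation is already stratified by site, the term still belongs in the analysis.
- **MOAKS.** A site factor cannot be added to a chi-square or Fisher test. If site is to be accounted for, use a site-stratified test, for example Cochran–Mantel–Haenszel.
- **Text.** Reconcile the single-site statement in Data monitoring with the two centres in Design and setting.

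Cost: a second list from the same generator and one degree of freedom (81.4% against 81.5% if site explains nothing and is balanced over arms). Incomplete last blocks at two sites may leave the overall allocation slightly uneven. No change in sample size is needed.
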